### Recruitment

Participants will be recruited through a number of methods. The app will be listed in the iTunes Store and the listing will be optimised according to best practices for app store optimisation (e.g. ensuring the keywords are carefully selected, that the description is well written and that screenshots display the aspects of the app that users are most interested in [111–114]). Users will be encouraged to leave reviews, which may persuade others to download it [114, 115]. We intend to promote the app through organisations such as the Department of Health and Public Health England, and mHealth (mobile health) directory web sites (e.g. ourmobilehealth.co.uk, myhealthapps.net), alcohol-reduction online forums (e.g. Club Soda) and the UCL App Lab service that promotes apps to all of the staff and students at UCL.

### Procedure

Each participant, on downloading the app, will be asked to read the participant information sheet and provide informed consent. Before being able to access the content of the app participants are asked to provide socio-demographic data, indicate their reason for using the app (interested in drinking less alcohol or just browsing), provide their e-mail address for the 1-month follow-up questionnaire and complete the full AUDIT questionnaire. At this point, all participants who meet the inclusion criteria will be randomised to one of 32 unique experimental conditions (see Additional file 2: Table S2) in a block randomisation method. After this they are provided with their AUDIT score and informed of their ‘AUDIT risk zone’. From this point onwards, the app differs for the different experimental conditions. Participants who do not meet all of the inclusion criteria can still use the app and will be allocated to a separate, non-experimental condition that has the ‘high’ version of each intervention module for engagement and app rating purposes.

One month after downloading the app, the app will automatically deliver a follow-up questionnaire. If this is not completed, email reminders will be sent at periodic intervals (1 day and 1 week). The follow-up questionnaire consists of the AUDIT and questions regarding usability.

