### Intervention

Drink Less is an app available for iOS devices that is designed to support a user who is interested in cutting down their alcohol consumption. The iOS (Apple’s operating system) was chosen to avoid issues of fragmentation associated with Android [107] and because there tends to be a greater retention rate for apps amongst iPhone users compared with Android [108]. There was a pragmatic, methodological need to structure the app around an activity that would engage all users and allow experimental manipulation of other supporting modules. Thus, the app asks all users to set a goal to which they would like to reduce their alcohol consumption. The app then offers them access to a variety of modules and tools to help them achieve their goal. The app was interactive though there was no human component to its functionality. The content of these five intervention modules is described in detail in Additional file 1: Table S1. The ‘high’ version of each intervention module contained the BCTs or intervention component hypothesised to be effective. The ‘low’ version of each intervention module lacked the BCTs or intervention component being assessed and, where possible, were based on controls in equivalent studies.

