### Study sample

Participants will be included in the analysis if they have downloaded the app onto an iOS smartphone or tablet, are 18 years of age or over, live in the United Kingdom and have an AUDIT score of 8 or above (indicative of excessive alcohol consumption), have confirmed that they are making an attempt to reduce their drinking (responded “Interested in drinking less alcohol”, not “Just browsing” to “Why are you using this app?”), and provided an email address.

This study will recruit 672 participants and have more than 80 % power (with alpha at 5 %, 1:1 allocation and a two-tailed test) to detect a mean change in alcohol consumption of 5 units between the high and low condition for each intervention module [109]. This assumes a mean of 27 weekly units at follow-up in the control group, a mean of 22 units in the intervention group and a SD of 23 units for both (d = 0.22), and rounds up the sample size to the nearest multiple of 32 to ensure all cells are balanced. The estimated effect size is large (comparable with that of a face-to-face brief intervention [5]) and may be considered somewhat unrealistic for a module within a digital intervention. However, in the event of a ‘non-significant’ result, we plan to calculate a Bayes factor to establish the relative likelihood of the null versus the experimental hypothesis given the data obtained [110]. This will permit a relative judgment for the purposes of screening about whether the inclusion of the module in a future app would be more likely than not to have an effect on alcohol consumption.

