### Outcome measures

The primary outcome measure is change in past week consumption of alcohol; calculated from the AUDIT-C score at baseline and 1-month follow-up [109]. Secondary outcome measures will be i) change between baseline and follow-up on the full AUDIT score ii) app usage data (user sessions per day, screen views per day, screens per session, session duration and session instances, user retention), and iii) usability ratings for the app (a) how helpful did you find Drink Less? b) how easy did you find Drink Less to use? c) how satisfied are you with Drink Less? d) how likely are you to recommend Drink Less to a friend?). An intention-to-treat approach will be used such that those who are lost to follow-up will be retained in the primary analysis and assumed to be drinking at baseline levels. The full 10-item AUDIT assesses alcohol consumption (AUDIT-C), harmful drinking and alcohol dependence [116]. The AUDIT has been used in other trials for assessing alcohol consumption and related harms [117].

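### The only source of the primary outcome is delivered first inside the intervention app, so response may follow app engagement and differ by module, with non-responders scored as no change

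*Protocol article*

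**What the plan says.** Protocol article, Procedure: "One month after downloading the app, the app will automatically deliver a follow-up questionnaire". It continues: "If this is not completed, email reminders will be sent at periodic intervals (1 day and 1 week"). The questionnaire consists of the AUDIT and usability questions. Every trial participant gives an email address before randomisation, with the one-month questionnaire as its stated purpose; an address is also an inclusion criterion (Study sample).

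Outcome measures: the primary outcome is "change in past week consumption of alcohol; calculated from the AUDIT-C score at baseline and 1-month follow-up". Secondary outcomes include app usage, with user retention among the measures. People lost to follow-up stay in the primary analysis at their baseline drinking level.

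Analysis: the factorial ANOVA tests module effects on primary and secondary outcomes, so retention is tested by module. The section accepts that those who respond well to the intervention are more likely to be retained, and calls the no-change rule conservative. Sensitivity analyses use responders only and imputation from baseline characteristics.

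Discussion: the authors expect high attrition, plan reminders and incentives, and gave goal-setting to everyone partly to keep users of the low versions engaged.

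**The concern.** The first attempt to obtain the primary outcome runs through the intervention being tested. Someone still opening the app is asked on the day. Someone who has stopped using or deleted it may be reached only by the email a day later, or the second one at a week. Whether a person responds, by which route and when can therefore follow engagement, which randomisation does not balance and which a module may alter.

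That would matter less if missing outcomes were handled neutrally. Here each non-responder contributes a change of zero, so a gap in response between the high and low levels of a module becomes a gap in mean change. The trial is a screening experiment: a module could be carried forward, or dropped, partly because of who answered. The Bayes factor planned after a non-significant result would use the same contrast and gives no protection.

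**Working it through.** **The plan's own figure.** Inputs from Study sample: a total of 672; "more than 80 % power (with alpha at 5 %, 1:1 allocation and a two-tailed test"); a target difference of 5 units per week for every module; means of 27 and 22 units; and "a SD of 23 units for both (d = 0.22").

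- n per level = 2 × (1.960 + 0.842)² × 23² / 5² = 332.2, taken up to 333; total 666; next multiple of 32 is 672.
- At 336 per level, SE = 23 × √(2/336) = 1.77 units and power is 80.4%.

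The stated size reproduces and does not depend on this point.

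**How response enters the contrast.** Let pH and pL be the response rates at the high and low levels, and RH and RL the mean reductions among responders. With zero assigned to non-responders:

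observed difference = pH × RH − pL × RL.

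Suppose the module has no effect on drinking and responders at both levels reduce by the same R. Then:

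spurious difference d = R × (pH − pL).

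This is an artefact only if the additional non-responders at one level reduced their drinking much as responders did but are coded as unchanged. The chance of a significant result is Φ(d/SE − 1.96) + Φ(−d/SE − 1.96).

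R, pH and pL are assumptions, because the article gives none of them:

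| R (units) | pL | pH | d (units) | Chance of p < 0.05 |
|---|---|---|---|---|
| 3 | 25% | 30% | 3 × 0.05 = 0.15 | 5.1% |
| 5 | 25% | 35% | 5 × 0.10 = 0.5 | 5.9% |
| 10 | 25% | 35% | 10 × 0.10 = 1.0 | 8.7% |
| 5 | 50% | 70% | 5 × 0.20 = 1.0 | 8.7% |
| 10 | 50% | 70% | 10 × 0.20 = 2.0 | 20.3% |

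The error rate stays below 9% unless both the gap and the responders' reduction are large. If the low level responds more, d has the opposite sign and works against the module. The SD of 23 is the plan's follow-up value; a change score with many zeros would have a different SD, so the last column is illustrative.

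**What this says about the no-change rule.** Under equal response it pulls the contrast towards zero, as the Analysis section intends. When response is higher at the high level it can create a difference, so the rule is conservative only if response does not follow allocation.

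**The case against.** The strongest reply is that follow-up does not rest on the app alone. Every participant's address is held from before randomisation, the first email goes after one day, the same reminder rule applies in all arms, and incentives are offered. Whether the email links directly to the form, and how long the window stays open, are details that a condensed article may leave to the full protocol; their absence is not counted here. All of that stands, and it makes a large gap less likely. It does not make the two routes equal: the person still using the app gets a prompt on the day plus reminders, while the person who has left it may get the reminders only.

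A second reply is that the sensitivity analyses would reveal the problem. In part they would: in the illustration above the responders-only contrast is zero, so disagreement with the primary result would be a warning. But the primary result is the no-change analysis, and imputation from baseline characteristics takes no account of engagement after randomisation.

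Third, no differential response has been shown, and the modules are intended to reduce drinking, not to change app use. Both are true. The point is that app use may change by module and is tested as an outcome.

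**Conclusion.** The concern holds in a limited form. First delivery inside the app may make response differ by module level, and the no-change rule would turn that difference into a shift in the primary contrast. Under the assumed ranges the shift is 0.15 to 2.0 units against the 5-unit target; the true size and direction are unknown. The case for changing the plan is that the safeguard is cheap, not that bias has been demonstrated.

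Three stronger readings are not supported:

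- **Timing from download biases the module comparisons.** Download precedes randomisation, so the scheduled date cannot depend on the module. A delay before registration would shorten exposure, but not selectively by module.
- **Email respondents report a materially different period.** The first email comes at one day; one week is the second reminder. Nothing in the article suggests that a shift of this order biases a past-week measure.
- **The high self-monitoring version gives a recall aid at follow-up that the low version lacks.** The article says that low versions "lacked the BCTs or intervention component being assessed", but the module content sits in an additional file not available here. Nothing states that drinking records are visible or consulted during the questionnaire. Any figure for such an effect would rest on invented under-reporting rates, so this remains speculation.

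**What to change.** On the due date, counted from randomisation, email every randomised participant a link to one questionnaire that can be completed without the app. Have the in-app prompt open the same form. Keep the 1-day and 1-week reminders for all non-completers. Log the channel and completion date, and report response, channel and date by level of each module, so that readers can see whether the no-change rule acted evenly.

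Counting from randomisation instead of download is minor tidying: it standardises exposure and does not remove a between-module bias.

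Cost: one web form, one extra email per participant to an address already held, a change to the timer's start, and possibly slightly fewer in-app completions. No additional participants are needed and the sample size of 672 is unaffected. Response will still depend somewhat on engagement, but less than under the present sequence.

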### Measures

#### Baseline measures

AUDIT score; socio-demographic assessment (age, gender, ethnicity, level of education, employment status and whether they are a current smoker).

### Outcome measures

The primary outcome measure is change in past week consumption of alcohol; calculated from the AUDIT-C score at baseline and 1-month follow-up [109]. Secondary outcome measures will be i) change between baseline and follow-up on the full AUDIT score ii) app usage data (user sessions per day, screen views per day, screens per session, session duration and session instances, user retention), and iii) usability ratings for the app (a) how helpful did you find Drink Less? b) how easy did you find Drink Less to use? c) how satisfied are you with Drink Less? d) how likely are you to recommend Drink Less to a friend?). An intention-to-treat approach will be used such that those who are lost to follow-up will be retained in the primary analysis and assumed to be drinking at baseline levels. The full 10-item AUDIT assesses alcohol consumption (AUDIT-C), harmful drinking and alcohol dependence [116]. The AUDIT has been used in other trials for assessing alcohol consumption and related harms [117].

### Analysis

A factorial between-subjects ANOVA will be conducted to assess main and interactive effects of the five intervention modules on the primary and secondary outcomes. In a sensitivity analysis, ANCOVAs will also be conducted to adjust for any chance imbalances in drinking and socio-demographic characteristics (gender, age, ethnicity, level of education, employment status, AUDIT score, AUDIT-C score).

On the basis of the intention-to-treat principle, individuals who are not followed up (non-responders) will be retained in the analyses and assumed they drinking at same levels as baseline. Sensitivity analyses will be conducted i) among only those who completed the follow-up questionnaire (responders) and ii) by imputing missing data from baseline characteristics. The intention-to-treat principle is often used in digital public health interventions [118–120] and is a conservative approach to ensure effect sizes are not over-estimated as participants who respond well to the intervention are more likely to be retained.

In the event of a non-significant main effect of an intervention module, Bayes factors will be calculated with the alternative hypotheses conservatively represented in each case by a half-normal distribution (online calculator: http://www.lifesci.sussex.ac.uk/home/Zoltan_Dienes/inference/Bayes.htm). In an alternative hypothesis represented by a half-normal distribution, the standard deviation of a distribution can be specified as an expected effect size, which means plausible values have been effectively represented between zero and twice the effect size, with smaller values more likely. The expected effect size for the primary calculation of Bayes factors will be the same as for the power calculation (d = 0.22). In a sensitivity analysis, we will also calculate Bayes factors for a smaller effect (reflecting a reduction of 3 units per week, d = 0.13).

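### The primary analysis of change in weekly units is unadjusted, which gives up precision the baseline data would supply, and the stated power fits the change score only under an unstated correlation

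*Protocol article*

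**What the plan says.** All references are to the Protocol article.

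- **Outcome measures:** "The primary outcome measure is change in past week consumption of alcohol; calculated from the AUDIT-C score at baseline and 1-month follow-up". People lost to follow-up stay in the primary analysis at their baseline level, so their change is zero.
- **Analysis:** "A factorial between-subjects ANOVA will be conducted to assess main and interactive effects of the five intervention modules". No covariate is named for this model.
- **Analysis, on adjustment:** "In a sensitivity analysis, ANCOVAs will also be conducted to adjust for any chance imbalances in drinking and socio-demographic characteristics". The listed covariates include the AUDIT and AUDIT-C scores.
- **Procedure:** before randomisation every participant must "complete the full AUDIT questionnaire", which contains AUDIT-C.
- **Study sample:** the 672 participants are said to "have more than 80 % power" for a 5-unit difference per module, "with alpha at 5 %, 1:1 allocation and a two-tailed test". On the inputs: "This assumes a mean of 27 weekly units at follow-up in the control group, a mean of 22 units in the intervention group", with an SD of 23 in both groups. Neither an SD of change nor a correlation between baseline and follow-up is given.

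**The concern.** Two things do not fit together.

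First, the model that uses the baseline value as a covariate is never less precise than the change score when the two SDs are equal. The data for it exist for everyone, yet it is only a sensitivity analysis. The article itself concedes that its target effect may be unrealistic for a single app module and that recruitment may be hard, so precision that costs nothing is worth having. The Bayes factors planned for non-significant modules also depend on the standard error of each module effect.

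Second, the sample size is worked out for one quantity (weekly units at follow-up) and the test is made on another (change in weekly units). The two have the same SD only under a particular correlation, which the article does not state.

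**Working it through.** **Inputs.** From Study sample: difference 5 units, SD 23 at follow-up, two-sided alpha 5%, 1:1 allocation, N = 672, so 336 per level of each module. Assumed, because the article does not give them: the same SD of 23 at baseline, and rho from 0.3 to 0.8.

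**Step 1. Reproduce the plan's figure.** n per level = 2 × (1.960 + 0.842)² × 23² / 5² = 332.2, so 333. The total is 666, and the next multiple of 32 is 672. Power with 336 per level and SD 23 is 80.4%. The stated sample size and power reproduce, for the SD of follow-up values.

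**Step 2. Full follow-up, by analysis.** With equal SDs:

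- SD of change = 23 × √(2(1 − rho)). This equals 23 only when rho = 0.5.
- Residual SD with baseline as covariate = 23 × √(1 − rho²).
- Variance ratio, adjusted to change = (1 + rho)/2, which is below 1 for every rho below 1.

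| rho | SD of change | Adjusted SD | Power, change | Power, adjusted |
|---|---|---|---|---|
| 0.3 | 27.2 | 21.9 | 66% | 84% |
| 0.4 | 25.2 | 21.1 | 73% | 87% |
| 0.5 | 23.0 | 19.9 | 80% | 90% |
| 0.6 | 20.6 | 18.4 | 88% | 94% |
| 0.7 | 17.8 | 16.4 | 95% | 98% |
| 0.8 | 14.6 | 13.8 | 99.4% | 99.7% |

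At rho 0.5 the total needed for 80% power is 666 for the change score and 500 for the adjusted model.

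**Step 3. Under the planned missing-data rule.** Let q be the proportion followed up, with loss unrelated to outcome and no mean change at the low level. Setting the rest to baseline has three effects:

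- The module effect shrinks to 5q.
- The correlation rises to q × rho + (1 − q).
- Each variance gains about 12.5 × q(1 − q), because in the high group responders and non-responders have different means.

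For rho 0.5 and q = 0.8, the effect is 4 units and the correlation is 0.60. SD of change = √(529 × 2 × 0.40 + 2) = 20.6. Adjusted SD = √(529 × (1 − 0.36) + 2) = 18.5.

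| rho among responders | Follow-up | Power, change | Power, adjusted |
|---|---|---|---|
| 0.5 | 80% | 71% | 80% |
| 0.5 | 60% | 58% | 65% |
| 0.5 | 50% | 51% | 56% |
| 0.3 | 80% | 57% | 71% |
| 0.6 | 80% | 80% | 87% |
| 0.7 | 60% | 80% | 83% |

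The adjusted model still gains, but less. The rho at which the change score reaches about 80% moves from 0.5 with full follow-up to about 0.6 at 80% follow-up and 0.7 at 60%.

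**The case against.** The case for leaving the plan alone is respectable. The unadjusted ANOVA on change is unbiased under randomisation. The adjusted analysis is already planned, expressly for chance imbalance in drinking, so the dispute is only over which of two planned analyses is primary. The gain depends on a rho that nobody can read from the article, and at 0.7 or above it is about 2 points or less with full follow-up. High attrition is expected, and the dilution from setting missing values to baseline costs more power than the choice of model. The trial is a screening experiment with Bayes factors as a second line. A condensed article may also leave the correlation to a fuller document.

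Most of this stands, and it limits the point to efficiency and the basis of the power figure. It does not remove the point: the article does fix the primary model, and it does attach its SD to follow-up means while testing change.

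Three stronger readings are tempting and are not supported:

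- **That the trial is underpowered on this ground.** Above rho 0.5 with full follow-up, the planned test has more power than stated.
- **That the covariate list is wrong because AUDIT contains AUDIT-C and weekly units are not listed.** Weekly units are calculated from AUDIT-C, so it is a close stand-in, and overlap between covariates does not harm the estimate for a randomised module.
- **That an SD of 23 would be a safe basis for the adjusted model at any rho.** Under the missing-data rule it is not: at rho 0.3 with 80% follow-up, adjusted power is 71%.

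**Conclusion.** The concern holds as a matter of efficiency and of the power statement's basis, not of validity. With equal SDs at both times and full follow-up, adjusting for baseline in the primary model would raise power for 5 units by about 18 points at rho 0.3, 10 at 0.5, 2 at 0.7 and under 1 at 0.8. With missing values set to baseline and rho 0.5, the gain is about 9 points at 80% follow-up, 7 at 60% and 5 at 50%.

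The power claim is correct arithmetic for follow-up values. For the change score with complete follow-up it needs a rho of at least about 0.5, and a higher rho once follow-up is incomplete. Since rho is assumed throughout, the size of the loss is a range and not an estimate.

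**What to change.** In Analysis, make the primary model a factorial ANCOVA: weekly units at follow-up (or change in them) on the five effect-coded modules, with baseline weekly units as a prespecified covariate. Keep the unadjusted ANOVA as the sensitivity analysis.

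In Study sample, state the rho or SD of change behind the power figure, and say that it assumes full follow-up. Do not describe SD 23 as conservative without that condition.

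The cost is a sentence in each section and no new data. The dilution caused by setting missing values to baseline is a separate matter that this change does not cure.

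### Assuming that non-responders drink at baseline level does not ensure against over-estimation: if response differs by module level, the primary analysis can be biased in either direction

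*Protocol article*

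**What the plan says.** The Outcome measures section fixes the rule: "those who are lost to follow-up will be retained in the primary analysis and assumed to be drinking at baseline levels". Every non-responder therefore enters the primary analysis with a change of zero. The Analysis section repeats the rule and says that the principle "is a conservative approach to ensure effect sizes are not over-estimated", because people who do well on the intervention are the ones more likely to stay. It adds two sensitivity analyses, one in responders only and one that imputes missing follow-up from baseline characteristics.

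Other parts of the article bear on whether response could differ by module:

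- Procedure: at one month "the app will automatically deliver a follow-up questionnaire". Those who do not complete it get email reminders at 1 day and 1 week.
- Outcome measures: the secondary outcomes include app usage, with "session duration and session instances, user retention", and the Analysis section tests secondary outcomes by module.
- Intervention: every user sets a goal for cutting down.
- Discussion: high attrition is expected, and incentives are mentioned as a way to reduce it.

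The article gives no expected response rate, no expected fall common to all users and no SD of change.

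**The concern.** A change of zero is neutral between the two levels of a module only if the same share of people is coded that way at each level, or if non-responders truly do not change. The reason given in the Analysis section, that good responders are retained, does not deal with response that differs between levels.

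The article makes such a difference plausible. The questionnaire arrives through the app, so a module that keeps people using the app may also raise the share who answer. A fall in drinking at both levels is plausible too, because all analysed users say they want to drink less and all set a reduction goal. The level with more responders then contributes more non-zero falls and looks better, whatever the module does to drinking.

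The trial is a screening experiment that chooses modules for a later app. A module could be kept because it improves questionnaire return, or dropped because its effect is diluted or because its high version lowers response. The Bayes factors planned for non-significant modules would be computed from the same estimates. A reader who trusts the word 'ensure' would not look for the first of these errors.

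**Working it through.** **The plan's own figure.** The Study sample section states "This study will recruit 672 participants and have more than 80 % power", "with alpha at 5 %, 1:1 allocation and a two-tailed test", for "a mean of 27 weekly units at follow-up in the control group, a mean of 22 units in the intervention group", with SD 23 in both groups.

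- n per level = 2 × (1.960 + 0.842)² × 23² / 5² = 332.2, so 333. The total is 666, which rounds up to 672 as a multiple of 32.
- With 336 per level, SE = 23 × √(2/336) = 1.77, z = 5/1.77 = 2.82 and power = 80.4%.

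The sample size reproduces and is not in dispute. It makes no allowance for the zeros.

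**Bias of the rule.** Let r be the response share, m the mean fall among responders and q the true mean fall among non-responders, with H and L for the high and low level.

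- Expected estimate: rH·mH − rL·mL.
- True difference: [rH·mH + (1 − rH)·qH] − [rL·mL + (1 − rL)·qL].
- Bias: (1 − rL)·qL − (1 − rH)·qH.

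For a module with no effect on drinking and the same q at both levels, the bias is q × (rH − rL). It is zero if response is equal or if q = 0. It reaches m × (rH − rL) if non-responders fall as much as responders.

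**Equal response.** Suppose a true effect T applies to everyone. The estimate is then r × T, so 5 units becomes 2.5 at 50% response and 1.5 at 30%. The variance per level is r·s² + r(1 − r)·m². At 50% with s = 23:

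- Low-level fall 0, high-level fall 5: variances 264.5 and 270.75, SE = √(535.25/336) = 1.26, z = 1.98, power 51%.
- Low-level fall 5, high-level fall 10: variances 270.75 and 289.5, SE = √(560.25/336) = 1.29, z = 1.94, power 49%.

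**Unequal response, module with no effect.** Assumptions: q = m (the upper end), 336 per level, two-sided 5% test. The first rejection rate uses a change SD of 23. The second uses 17.8 = 23 × √(2 × (1 − 0.7)), for an assumed baseline to follow-up correlation of 0.7.

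| Response, high v low | General fall m | False effect (units) | Rejection, SD 23 | Rejection, SD 17.8 |
|---|---|---|---|---|
| 60% v 50% | 3 | 0.3 | 5.6% | 6.0% |
| 60% v 50% | 5 | 0.5 | 6.6% | 7.7% |
| 60% v 50% | 10 | 1.0 | 11.3% | 15.1% |
| 70% v 50% | 3 | 0.6 | 7.2% | 8.7% |
| 70% v 50% | 5 | 1.0 | 11.1% | 15.2% |
| 70% v 50% | 10 | 2.0 | 29.0% | 42.6% |

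Worked row (60% v 50%, m = 10, SD 23): the variances are 0.6 × 529 + 0.24 × 100 = 341.4 and 0.5 × 529 + 0.25 × 100 = 289.5. SE = √(630.9/336) = 1.37, z = 1.0/1.37 = 0.73, and the rejection rate is 11.3%. Simulations of 5,000 runs agree: 6.2% for 60% v 50% with m = 5 and 29.2% for 70% v 50% with m = 10, both at SD 23. With equal response, or with m = 0, the rate stays at 5%.

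**Real effects.** With q = m, the estimate is rH·(m + T) − rL·m.

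- 70% v 50%, m = 10: a true 3 gives 0.7 × 13 − 0.5 × 10 = 4.1, and a true 5 gives 5.5. Both are over-estimates.
- 60% v 50%: a true 5 gives 3.5 (m = 5) or 4.0 (m = 10). Both are still under-estimates.
- 50% at the high level v 60% at the low level, m = 10: a true 5 gives 1.5, and a true 1 gives −0.5.

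**The case against.** Three stronger readings are tempting, and the documents support none of them.

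**Any module effect on retention becomes a false drinking effect.** This needs non-responders to have fallen as well. If they truly stay at baseline, zero is the right value and there is no bias. The article's own rationale, that people who do well are more likely to be retained, points partly that way, and nothing in the documents settles it.

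**The conservative property does not exist.** It does hold when response is equal, and attenuation remains the net result for a true 5-unit effect with a 10-point gap in favour of the high level. What fails is the assurance that over-estimation cannot occur.

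**The inflation is large.** That rests on a large general fall. The only level given is a mean of 27 units at follow-up in the control group, so a fall of 10 would imply a baseline of about 37. With falls of 3 to 5 units and a 10-point gap, rejection is about 6% to 8%. The documents also give no evidence that response will differ. Listing retention as an outcome does not show that it will, and the email reminders and incentives reach people who no longer open the app, so they may narrow any gap.

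It also counts for the plan that responder-only and imputation analyses are already included, and that modules kept by mistake go into a later definitive trial as part of the package. These points lower the severity. They do not rescue the claim: the other analyses are secondary, no rule says what happens if they disagree with the primary one, and a module wrongly dropped is not tested again in that package.

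**Conclusion.** The statement in the Analysis section is wrong as written. Assuming baseline drinking attenuates effects when response is equal at both levels. When response differs and non-responders share at least part of a general fall, it can bias a module's effect in either direction. For a module with no effect, the false effect is at most the general fall times the difference in response: 0.3 to 1.0 units for 60% v 50% and falls of 3 to 10 units, with type I error of about 5.6% to 11%. At 70% v 50%, type I error is 11% for a fall of 5 and 29% for a fall of 10. These figures assume a change SD of 23 and 336 per level, and a smaller SD raises the error rates. The mechanism is certain. Its size in this trial is not, because response, general fall and SD of change are all assumed.

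A reader might infer that the primary analysis must be replaced by imputation. The documents do not require that. Missing-at-random cannot be tested, and if non-responders do worse, as the article suggests, such imputation would credit them with falls they did not have. The point is of moderate severity and concerns what may be claimed and concluded.

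**What to change.** 1. Delete the claim that the rule ensures effects are not over-estimated. State instead that it attenuates effects under equal response and can bias them either way when response differs by level.
2. Report the follow-up response at the high and low level of each of the five modules.
3. In the imputation analysis already planned, add the five module factors and, where available, app usage to the baseline characteristics.
4. Where response differs by level, do not call a module effective or ineffective on the baseline-carried-forward result alone. Require agreement with the imputation analysis.

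Making imputation primary, with the present rule as a sensitivity analysis, is an option and not a necessary correction.

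The cost is a change of wording and a little more analysis, with no new data: app usage is already an outcome. The downside is that some modules will get a less clear-cut conclusion.
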